**Electronic Health Record data**

To evaluate the 2018–2021 NYULH EHR data, baseline characteristics and outcomes will be summarized descriptively and graphically. Continuous variables will be summarized with means, standard deviation, medians, and ranges. Categorical variables will be analyzed with frequency distributions. We will group patients to create variables as follows: group 1 will contain patients with diagnosis of HTN and who have a controlled BP reading (systolic blood pressure [SBP] <130 and diastolic blood pressure [DBP] <80) based on mean of the last two BP readings; group 2 will contain patients with a diagnosis of HTN who have an uncontrolled BP reading (SBP≥130 or DBP ≥80) based on the mean of the last two BP readings; group 3 will contain patients without a diagnosis of HTN who have at least 2 uncontrolled BP readings; and group 4 will contain patients without a diagnosis of HTN who have at least 2 elevated BP readings (120≤SBP≤129 and DBP ≤ 80). To examine the associations between the variables, the chi-square test for categorical variables and the Kruskal-Wallis test for ordinal or interval variables will be used. *P*-values of these tests which are less than or equal to the specified significance level will be used to examine associations between variables. Two 2-way contingency tables will examine Race by all other variables and Group by all other variables. A three-way contingency table will be conducted to examine Hypertensive diagnosis and Race by all other variables. The table will examine proportions across the two main variables of interest (Hypertension diagnosis and Race). Lastly, we will conduct a multinomial logistic regression model for our nominal outcome variable, group, with *P*-values and odds ratios to examine the association between categories of groups.

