##### NYU health system epic EHR (patient data)

A descriptive analysis of 2018–2021 NYULH EHR data, collected from the Epic platform, will help to characterize HTN burden and risk factors among patients within NYULH primary care practices. Measures explored in the datasets will include sociodemographic and clinical factors. Sociodemographic variables include race, health insurance status, age, sex, and NYC borough for current patients within NYULH practices. Clinical variables include medications (i.e.: HTN classes and dosages), medical comorbidity (i.e., diagnosis of diabetes, obesity, stroke, and/or chronic kidney disease), Charlson Comorbidity score, social history (i.e., smoking and drinking status), and patients’ clinic visit history. In addition, HTN diagnosis and BP readings (2018 to 2021) will be extracted from the EHR to categorize the patients in order to explore their HTN risk levels. Patients will be categorized into four groups: (1) HTN diagnosis with controlled BP; (2) HTN diagnosis with uncontrolled BP; (3) no HTN diagnosis and at least 2 uncontrolled BP readings (1 week apart); and (4) no HTN diagnosis and at least 2 elevated BP readings (1 week apart).

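### EHR groups 3 and 4 can both hold the same undiagnosed patient, so the outcome of the planned multinomial model is not uniquely defined; the effect is confined to a descriptive secondary-data analysis.

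*Protocol article*

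**What the plan says.** The section Electronic Health Record data gives the group rules.

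- Groups 1 and 2 (diagnosed) are split by one value per patient. The rule for the first is "controlled BP reading (systolic blood pressure [SBP] <130 and diastolic blood pressure [DBP] <80) based on mean of the last two BP readings". The rule for the second is "uncontrolled BP reading (SBP≥130 or DBP ≥80) based on the mean of the last two BP readings".
- Group 3 (undiagnosed): "group 3 will contain patients without a diagnosis of HTN who have at least 2 uncontrolled BP readings". No threshold is restated here, so the group 2 cut-off is the only definition of uncontrolled in the article.
- Group 4 (undiagnosed): "group 4 will contain patients without a diagnosis of HTN who have at least 2 elevated BP readings (120≤SBP≤129 and DBP ≤ 80".

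The earlier section NYU health system epic EHR (patient data) sets the window: "HTN diagnosis and BP readings (2018 to 2021) will be extracted from the EHR to categorize the patients". It adds a spacing condition, for example "3) no HTN diagnosis and at least 2 uncontrolled BP readings (1 week apart". The analysis section does not repeat that condition.

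The classification is then used as an outcome: "we will conduct a multinomial logistic regression model for our nominal outcome variable, group". It also forms one margin of a two-way table against all other variables, with chi-square or Kruskal-Wallis tests. Neither section ranks the groups or excludes group 3 patients from group 4.

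**The concern.** A multinomial logistic model assigns each subject probabilities over categories that sum to one, so each subject must have exactly one observed category. A chi-square test on a table by group likewise assumes that nobody is counted twice. Groups 1 and 2 meet this requirement because one summary value is split at complementary cut-offs. Groups 3 and 4 do not, because each is filled by counting individual readings, and the two reading definitions share a boundary value.

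An analyst following the text would find some undiagnosed patients who qualify for both groups. Whoever writes the code must then choose: group 3 first, group 4 first, most recent readings, or duplicate rows. Each choice gives different group sizes and different odds ratios for groups 3 and 4, and the article offers no basis for choosing.

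**Working it through.** The article states no figure on this point, so there is nothing to reproduce. The rules were applied as written.

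**Inputs from the article**

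- Uncontrolled reading: SBP ≥130 or DBP ≥80.
- Elevated reading: 120 ≤ SBP ≤ 129 and DBP ≤80.
- Group 3: no diagnosis and at least 2 uncontrolled readings.
- Group 4: no diagnosis and at least 2 elevated readings.

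**Step 1: overlap at the boundary**

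A reading is in both categories if SBP is 120-129, DBP ≤80, and (SBP ≥130 or DBP ≥80). SBP ≥130 is impossible within 120-129, so DBP must be both ≤80 and ≥80, which means exactly 80. That leaves 10 integer readings, 120/80 to 129/80. Enumerating all integer readings with SBP 80-220 and DBP 40-130 gives the same 10. Two readings of 125/80 a week apart therefore satisfy groups 3 and 4 on the same data. With DBP <80 in group 4 the number falls to 0.

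**Step 2: overlap through the count rule**

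Take an undiagnosed patient with 135/85, 138/86, 124/75 and 126/76.

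- Uncontrolled: 135/85 and 138/86, count 2, so group 3 is met.
- Elevated: 124/75 and 126/76, count 2, so group 4 is met.

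No reading is ambiguous, and changing the boundary to DBP <80 leaves the result unchanged. Spacing the readings a week apart does not remove it either. Once the boundary is corrected, this route needs at least 2 + 2 = 4 readings.

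**Step 3: how often this could happen (illustrative)**

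The article gives neither readings per patient nor a BP distribution, so these inputs are assumptions:

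- population mean for undiagnosed patients 120-124/74-76 mmHg;
- between-person SD 12/8 and within-person SD 8-10/6-7;
- systolic-diastolic correlation 0 or 0.6;
- normal readings rounded to integers, no digit preference, and every reading taken to meet the spacing condition.

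Two shares were simulated: the patients in both groups divided by all undiagnosed patients, and the same patients divided by those meeting group 4.

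| Readings per patient | In both, of all undiagnosed | In both, of those meeting group 4 |
|---|---|---|
| 2 | about 0% | under 1% |
| 4 | 5-7% | about 30-40% |
| 6 | 17-21% | 54-69% |
| 10 | 34-41% | 71-87% |

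A second set of assumptions (between- and within-person SD both 8/6, means 122/75 to 130/79) used a third denominator, the patients meeting group 3 or group 4. The share in both was about 0% with 2 readings, 10-12% with 4, 37-47% with 8 and 51-64% with 12. Correcting only the boundary lowered these by about 2-4 percentage points at 4 or more readings. The count rule is therefore the main source of overlap.

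**Step 4: what the assignment choice does**

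If group 3 takes precedence, group 4 loses every patient in both groups. Under the first set of assumptions that is about 30-40% of group 4 with 4 readings per patient. If group 4 takes precedence, group 3 loses the same patients.

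**The case against.** The strongest reply is that single assignment is plainly intended. The article speaks of categorising patients into four groups and of one nominal variable, and a tie-break is a derivation detail that a condensed article may leave to the full protocol or analysis plan. That has some force for the count rule. It does not settle the matter, because the article does state the membership rules, and as stated they put the same patient in two groups. The boundary conflict is an inconsistency between two printed cut-offs and cannot be put down to condensation.

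The second reply is that little depends on this analysis. That stands. The EHR work is described as descriptive, the primary outcome is a tailored facilitation strategy, and qualitative findings are given priority and prevail where sources diverge. No efficacy endpoint in the article uses groups 3 and 4.

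Two stronger readings are tempting, and the article supports neither.

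- A reader might infer that the outcome is undefined for a large share of undiagnosed patients. The highest percentages are shares of group 4, not of all undiagnosed patients. With 2 readings per patient the overlap almost vanishes, and the article does not say how many readings patients have.
- A reader might infer that undiagnosed patients with uncontrolled BP, whom the triangulation step wants to capture, would be missed. Anyone with two qualifying uncontrolled readings meets group 3 whether or not group 4 is also met. They would be lost from group 3 only if the code let group 4 override it, and nothing in the article says it would.

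**Conclusion.** The point holds. As printed, groups 3 and 4 are not mutually exclusive, for two separate reasons: the shared value DBP = 80, and the counting of at least two readings without precedence. Both follow from the text by logic. The only interpretive step is to read uncontrolled in group 3 with the cut-off given for group 2, which is the sole definition available and matches the DBP <80 limit in group 1. The count-rule overlap does not depend on what happens at DBP = 80.

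The size is uncertain. It runs from about 0% to 34-41% of undiagnosed patients as readings per patient go from 2 to 10, and these figures rest wholly on assumed BP distributions. They ignore the one-week spacing, which can reduce the number of qualifying readings but does not remove the overlap. The consequence is limited to the group sizes, tables and odds ratios of one descriptive secondary-data analysis. It should still be settled before coding, because the multinomial model cannot be fitted as described until each patient has one category.

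**What to change.** For the analysis grouping only:

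1. Set the group 4 reading to 120 ≤ SBP ≤ 129 and DBP <80, so that it agrees with the article's own cut-offs for controlled and uncontrolled.
2. Define group 4 as no diagnosis, at least 2 elevated readings, and not meeting group 3.
3. Use one wording, including the one-week spacing, in both the EHR measures section and the EHR analysis section.

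Both of the first two changes are needed. The boundary change alone leaves the count-rule overlap. Precedence alone leaves 125/80 counted as elevated as well as uncontrolled, so a patient with one 125/80 and one 125/75 would enter group 4 on a reading that the article also calls uncontrolled.

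Classifying undiagnosed patients by the mean of their last two readings is not a clean alternative with the present cut-offs. Systolic readings of 129 and 130 average (129 + 130)/2 = 129.5, which with DBP <80 is neither elevated nor uncontrolled. It would work only if the elevated range were rewritten as 120 ≤ SBP < 130, and it would also drop the repeated-reading requirement.

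The cost is a sentence in the plan and a few lines of code. No new data are needed.

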## Methods

### Study design

#### Brief overview of the needs assessment for the clinic-community-based implementation program for hypertension control

The needs assessment for the program will be carried out between September 2020 and August 2023. The program will target Blacks with uncontrolled HTN followed in 27 primary care practices within the New York University Langone Health (NYULH) system. The program consists of two phases: (1) the pre-implementation phase, which comprises the needs assessment and refinement of the PF strategy, and (2) the implementation phase, which implements and evaluates a community-clinic linkage model. This model comprises three EBIs collectively termed PACE, which includes HBPM, NCM, and SDoH Support. Practice facilitators will assist each of the 25 primary care practices plus 2 pilot sites in the implementation of PACE (Fig. 1), in a step-wedged cluster randomized control trial design [45–48].

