## Conclusion

We describe a comprehensive needs assessment to understand hypertension management experiences of Black patients with uncontrolled HTN in NYC by collaborating with multiple clinic and community stakeholders to identify available capacities and supports for hypertension control for this group. Integration of stakeholders’ priorities, perspectives, and practices with the PACE program will improve adoption, sustainability, and the potential for scale-up. Findings will inform the development of a tailored PF strategy for implementing PACE into primary care settings for hypertension control to ensure intervention uptake and sustainment.

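### The planned EHR tables count Black patients with uncontrolled hypertension but do not describe them by any other variable, because the only three-way table is stratified by diagnosis, not by control group

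*Protocol article*

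**What the plan says.** The Brief overview of the needs assessment states the target: "The program will target Blacks with uncontrolled HTN followed in 27 primary care practices". The Conclusion repeats it, giving the purpose as to "understand hypertension management experiences of Black patients with uncontrolled HTN in NYC".

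The data analysis section on Electronic Health Record data then creates four groups. The first two divide diagnosed patients by the mean of their last two readings: "group 1 will contain patients with diagnosis of HTN and who have a controlled BP reading", and "group 2 will contain patients with a diagnosis of HTN who have an uncontrolled BP reading". Groups 3 and 4 hold patients without a diagnosis.

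The same section lists its tables. First, "Two 2-way contingency tables will examine Race by all other variables and Group by all other variables". Then comes the three-way table: "A three-way contingency table will be conducted to examine Hypertensive diagnosis and Race by all other variables". Its stratifiers are confirmed in the next sentence: "The table will examine proportions across the two main variables of interest (Hypertension diagnosis and Race"). Last comes a multinomial logistic regression with Group as outcome; its predictors are not named.

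Under Triangulation and synthesis of findings, patient-level determinants of control are among the constructs carried into the joint display. That display informs the practice facilitation strategy, which the Main outcome section makes the primary outcome.

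**The concern.** To tailor a strategy to Black patients with uncontrolled hypertension, one needs to see who they are (insurance, comorbidity, medication, visit history) and how they differ from Black patients whose pressure is controlled. That requires Race and control status to be held together while a third variable is examined. The plan constructs control status, but its one three-way table uses diagnosis, which cannot separate controlled from uncontrolled patients.

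The wording closely follows the plan for the CHS data. Diagnosis is a natural stratifier there, because the CHS measures list diagnosis, medication status and recent BP checking but no measured control. The EHR has BP readings, so the same limit does not apply.

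At stake is the EHR contribution to the joint display. Findings on determinants of control would come from a stratum that mixes controlled and uncontrolled Black patients, or from group summaries not separated by race.

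**Working it through.** The protocol gives no figure to reproduce here. The check is which planned table yields which quantity. Let V be any other extracted variable, such as insurance or diabetes.

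**Step 1: what each table provides**

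| Planned output | Black group 2 count | Distribution of V within Black group 2 |
|---|---|---|
| Race × V | Yes, when V is Group | No: pools groups 1 to 4 |
| Group × V | Yes, when V is Race | No: pools all races |
| Diagnosis × Race × V | Yes, when V is Group | No: groups 1 and 2 share the diagnosed stratum |
| Multinomial model for Group | Not its purpose | Not determined: predictors unnamed, and the output is odds ratios |

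So the count of Black patients in group 2 is available. Their profile is not, because no listed table is Group × Race × V.

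**Step 2: can the profile be recovered from the planned tables?** The protocol does not give the counts, so this is an illustration.

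Inputs:
- Assumed: 1,000 Black and 4,000 non-Black diagnosed patients.
- National control rates from the Background: 48.5% in Blacks and 55.7% in Whites. Applying the White rate to all non-Black patients is an assumption.
- Assumed: V present in 30% of each race and of each group.

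Margins:
- Black: group 1 = 0.485 × 1,000 = 485; group 2 = 1,000 − 485 = 515.
- Non-Black: group 1 = 0.557 × 4,000 = 2,228; group 2 = 4,000 − 2,228 = 1,772.
- With V: Black 0.30 × 1,000 = 300; non-Black 0.30 × 4,000 = 1,200.
- With V in group 2: 0.30 × (515 + 1,772) = 686 (rounded). With V in group 1: 300 + 1,200 − 686 = 814.

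Let b be the number of Black group 2 patients with V. Every planned table is unchanged for any b that satisfies:
- 0 ≤ b ≤ 515
- 0 ≤ 300 − b ≤ 485
- 0 ≤ 686 − b ≤ 1,772
- 0 ≤ 1,200 − (686 − b) ≤ 2,228

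The second condition gives b ≤ 300, and no condition raises the lower limit above 0. Hence b runs from 0 to 300, and the prevalence of V in Black group 2 from 0/515 = 0% to 300/515 = 58.3%.

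The non-Black conditions do not bind, so the limits come from the Black margins alone. For an assumed prevalence p up to 48.5%, the same Black margins keep the lower limit at 0, and they cap the upper limit at 1,000p/515.

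**Step 3: after the change.** A Group × Race × V table contains b itself, so the interval becomes one observed value.

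**The case against.** Several points on the other side have force.

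- **The tables do not ignore the target.** A reader might infer that no planned EHR table isolates Black uncontrolled patients, or that diagnosis is the only HTN status crossed with race. The documents do not support that: each two-way table includes Race × Group. Only the profile is missing.
- **Group 2 is not exactly the eligible population.** Study settings defines eligible patients by a diagnosis and one or more uncontrolled readings in a two-year window. Group 2 uses the mean of the last two readings. A Black patient with one high reading and a controlled recent mean is in group 1 yet meets the eligibility definition. A reader might therefore take the 48.5% control rate as the share of the Black, diagnosed stratum outside the target. That does not follow, since an unknown part of group 1 is eligible.
- **The model may include race.** A reader might infer that the regression pools all races. The text neither includes nor excludes race terms, and the parallel CHS model names Race as a predictor. A predictor list can reasonably be left to a fuller document.
- **The diagnosis table has a use.** The EHR analysis is meant to be broad: it "will help to characterize HTN burden and risk factors among patients within NYULH primary care practices". Triangulation also seeks undiagnosed patients, and the layout matches the CHS.
- **The EHR is one source of four.** Qualitative findings take precedence where sources diverge, and no trial estimate or error rate rests on this table.

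These points limit the claim and its weight. They do not supply the missing table. The stratifiers are named, and restated in the following sentence, so this is a stated choice and not merely a detail left out of a condensed article. The text does promise general descriptive and graphical summaries, but without committing to this one.

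**Conclusion.** The concern holds in a limited form: the planned tables give the number of Black patients with uncontrolled hypertension but no description of them by any other variable. This follows from the named stratifiers and needs no numerical assumption. It is worth correcting because that population and its determinants of control are the programme's focus.

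The 0% to 58.3% range shows only that the planned tables cannot determine the profile. It rests on assumed counts, national control rates and an assumed 30% prevalence, and it does not estimate an error in this health system. Group 2 is taken as the nearest EHR counterpart of the target, not as identical to it. The diagnosis stratum does not isolate uncontrolled patients under either definition.

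The effect is on the usefulness of one descriptive source. The documents do not support saying that the whole strategy would be tailored to the wrong patients.

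**What to change.** In the data analysis section on Electronic Health Record data:

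1. Add a three-way table of Group by Race by all other variables, so that Black group 1 and Black group 2 appear as separate columns. The diagnosis by Race table can stay for comparison with the CHS.
2. State that group 2 versus group 1 will be reported within Black patients, either by restricting the multinomial model to them or by including race-by-predictor terms.
3. Reconcile group 2 with the definition of eligible patients under Study settings, and say which of the two the profile is meant to describe.

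The variables are already to be extracted, so the cost is a few sentences and extra tabulation. The drawback is smaller cells than in the diagnosis table.

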##### Triangulation and synthesis of findings

Triangulation will be used to integrate the multiple data sources, in order to improve the understanding of the context in which PACE will be implemented in primary care practices in NYC. We will use a concurrent triangulation approach [49] to examine instances of data congruence and or incongruence. This will also help to strengthen our interpretation and ensure that we have captured all potential participants at risk in the community (informed by the CHS data) and those already in the NYU healthcare system but undiagnosed and uncontrolled. The focus group and interview discussions will help to inform our understanding of the quantitative data and collaboratively work with the various stakeholders to identify facilitators to implementation and derive potential solutions to contextual challenges during PACE implementation. Following best practices for mixed methods research [50], we will construct a joint display [51] that integrates the data sources. Constructs to be integrated include community and neighborhood characteristics, patient-level determinants of HTN control, organizational capacity for change, availability of resources to support change, and attitudes toward EBIs. Should the data be divergent, we will assign higher credence to the qualitative data which offer richer explanation about participants’ attitudes and behaviors [50]. We will incorporate best practices in data visualization to transform these large bodies of disparate data into timely, digestible, and actionable insights that will inform the PF strategy.

